**Figure 1 figure1:**
[figure not shown]
Screenshots of the mobile app. The information in the app is provided as text messages, graphics, and videos or by gamification and storytelling approaches. Screenshots taken on EMUI (version 12.0.0, Huawei).

The intervention content and mobile app were evaluated in a pretest [42]. In the pretest, the long-term unemployed participants (N=12) were asked to test the mobile app for 9 weeks, and feedback was recorded every 3 weeks. The intervention content and mobile app were modified as suggested by the participants.

### Randomized Controlled Intervention Study

#### Study Design

To elucidate the effectiveness of the designed intervention, a 2-armed parallel-designed RCT is conducted with the long-term unemployed of the rural areas of Germany. The study protocol has been approved by the ethics committee of the State Medical Chamber of Baden-Wuerttemberg, Germany (number F-2019-106), and registered in the German Clinical Trials Register (DRKS00024805).

The intervention group (n=100) receives information materials (eg, brochures) regarding healthy nutrition and physical activity behavior and has access to the DHI in the form of a mobile app (refer to the section Intervention Contents and Mobile App). The intervention period is set to be 9 weeks, as this has been shown to be in the range of adequate time spans for DHIs (usually between 4 and 12 weeks) [43-46]. At baseline, after 3 and 6 weeks of intervention, the participants in the intervention group are scheduled to visit the study center located in the affiliated social sector institution to attend additional face-to-face sessions regarding technical instructions on the mobile app, healthy nutrition, and physical activity behavior, respectively. The control group (n=100) will meet at baseline at the study center to receive information material in the form of, for example, brochures (same as the intervention group) but will not have access to the DHI and will not attend the face-to-face sessions regarding technical instructions, healthy nutrition, and physical activity behavior. In addition, all participants (intervention and control group) will visit the study center after 9 weeks of intervention for a joint conclusion and to receive an incentive of €50 (US $49.7). The group allocation will not be blinded, as this is not applicable to the study design. If possible, investigators analyzing the data will be unaware of the group assignment.

Recruitment is conducted via the social sector (eg, employment societies) of the rural regions in southwestern Germany, and participant recruitment started in March 2022. Recruitment will proceed until the required number of participants is reached or until the end of 2022. The inclusion criteria are long-term unemployment (defined as >12 months), between 18 and 67 years of age, and fluency in German. In addition, the participants must have access to a smartphone or tablet with Android (minimum version 6.0) or iPhone (minimum version 9.0) operating system. As the focus of this study is on rural areas, the affiliated social sector institutions must be located in rural areas. The long-term unemployed volunteers will be allocated randomly (Figure 2) to 1 of the 2 groups by a randomization list with a block size of 4, stratified to the social sector institutions, which accomplished the recruitment.

**Figure 2 figure2:**
[figure not shown]
Participant flow diagram. Interested participants will be assessed for eligibility, and participants not meeting the inclusion criteria will be excluded. Remaining participants will be randomized into two groups (intervention and control). The completion, withdrawal, and losses to follow-up will be monitored, and the effectiveness of the intervention will be assessed at baseline (T0), after intervention (T1), and at follow-up (T2) by questionnaire assessment.

#### Outcomes

The effectiveness of the DHI will be evaluated by self-reported questionnaire assessment in German at baseline (T0), after 9 weeks of intervention (T1) at the study center, and after a 3-month follow-up period (T2) by mail services. Physical activity is assessed using the International Physical Activity Questionnaire in the German short version. The International Physical Activity Questionnaire has been validated several times [47,48] and measures the duration (minutes) and frequency (days) of sitting, moderate physical activity, and vigorous physical activity during the last 7 days, which will be expressed in minutes per day.

The food frequency questionnaire (FFQ) is a revised version of the FFQ used in the German Health Interview and Examination Survey for Adults (DEGS) [49], which was validated by the study by Haftenberger et al [50]. The FFQ consisted of 68 questions regarding the consumption frequency and portion sizes of food items in the past 4 weeks. The food intakes assessed by the FFQ will be expressed as servings of the consumed food item per day, and a food-based diet quality score will be analyzed according to the study by Masip et al [51].

To elucidate the adherence of the participants, the use of the mobile app will be monitored throughout the study period, and the affinity to technological devices is assessed by questionnaires before the study. The usability and acceptance of the mobile app will be assessed according to the unified theory of acceptance and use of the technology model [52]. Therefore, qualitative interviews or focus groups with the participants will be conducted and analyzed by structured content analysis according to the method by Mayring [53] using MAXQDA (version 2022; VERBI GmbH).

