**Methods:**

The 9-week intervention aims to promote nutritional or physical activity behavior by improving drinking habits, increasing the consumption of fruits, vegetables, and whole grains, increasing daily step count, strengthening muscles, and improving endurance. The intervention design is based on the transtheoretical model and is implemented in a mobile app using the MobileCoach open-source platform. The effectiveness of the intervention will be elucidated by a 9-week, 2-armed, parallel-designed trial. Therefore, long-term unemployed will be recruited by employees of the German social sector institutions and randomized either to receive information brochures; the digital intervention in the form of a mobile app; and 3 face-to-face sessions regarding technical support, healthy eating, and physical activity (n=100) or to receive a control treatment consisting of solely the hand over of information brochures (n=100). The effectiveness of the intervention will be assessed using questionnaires at baseline, after 9 weeks in face-to-face appointments, and after a 3-month follow-up period by postal contact. The use of the mobile app will be monitored, and qualitative interviews or focus groups with the participants will be conducted. Incentives of €50 (US $49.7) will be paid to the participants and are tied to the completion of the questionnaires and not to the use of the mobile app or progress in the intervention.

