#### Statistical Analysis

Sample size calculation was conducted using G*Power (version 3.1.9.7, Heinrich Heine University Duesseldorf). As shown in a meta-analysis by Duan et al [54], the postintervention effect sizes of nutrition- and physical activity–related outcomes in patients with noncommunicable diseases in the intervention and control groups range widely from −1.11 to 6.40 (mean 0.85, SD 1.48) and −0.13 to 4.78 (mean 0.78, SD 1.77), respectively. As we suggested a lower adherence and thus a lower effect size in the targeted group in this study (long-term unemployed), we assumed the effect to be of medium size (Cohen *d*=0.5). With an alpha error of .05 and a power (1-β) of .80, a total sample size of 128 participants (n=64 per group) was calculated. In addition, a previously conducted pretest showed a high dropout of participants of approximately 33% after 9 weeks of treatment, defined as participants who did not reach the “action” phase according to Prochaska et al [33]. Thus, to take further potentially high dropout rates into account, we aim to include a total of 200 participants (n=100 per group) in this study.

To investigate the impacts of the intervention on the self-reported health outcomes assessed by the questionnaire, differences between the 3 data collection times (T0, T1, and T2) and between the 2 groups (intervention vs control) will be analyzed. To test for normal distribution, all data will be subjected to the Kolmogorov-Smirnov test. In case of normal distribution and homoscedasticity of variance (Mauchly’s sphericity test), time-dependent differences will be analyzed by repeated measurement analysis of variance with post hoc comparison by Bonferroni test. In case of nonparametric data, the Friedman test will be used, and the significance level will be corrected using Bonferroni correction. If a normal distribution is given, the differences between the 2 groups at 1 time point will be compared by 2-tailed *t* test. Otherwise, the data will be analyzed by Mann-Whitney *U* test. All differences will be considered statistically significant with *P* values <.05. Statistical analysis will be conducted using SPSS Statistics (version 28, IBM Corporation).

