
### Limitations

This study has some limitations. First, we did not adapt the intervention according to the multiphase optimization strategy, which maximizes the translation of research into effective practice [74]. However, we did run a pretest while developing the intervention to ensure the feasibility of the blended intervention. Second, the effectiveness of the intervention is based on questionnaires and, therefore, might be underlying a reporting bias. Further studies might be necessary to measure physiological adaptation to a healthier lifestyle, for example, by measures of health-related biomarkers, such as markers for metabolic diseases [75] or cardiovascular health [76]. Third, as the participants receive incentives, they might have been overly motivated to use the mobile app. To counteract a potential overestimation of the app use through the incentives, we instructed the participants that the incentives are only tied to the completion of the questionnaire and not to the use of the mobile app. Finally, although in previously conducted interviews (N=20), most of the long-term unemployed in the rural areas of southwestern Germany (75%) had smartphones and regularly used mobile apps on their devices ([name], unpublished data, February 2020), some may not and, therefore, cannot participate in this study. However, the ownership of smartphone devices is still rapidly growing [77]. Thus, we feel that a DHI with face-to-face appointments is a promising strategy to improve the health of long-term unemployed in the rural areas of Germany. At this point, it must also be emphasized that behavior change strategies may only address the secondary effects of long-term unemployment. In general, improving living conditions (eg, better financial support or social inclusion) may be a more comprehensive strategy for promoting health among the unemployed.

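### Change over time to T2 is confounded with the move from study-center to postal questionnaires, so T2 conclusions should rest on the comparison between arms

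*Protocol article*

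**What the plan says.** **Setting of collection.** The abstract (Methods) describes "questionnaires at baseline, after 9 weeks in face-to-face appointments, and after a 3-month follow-up period by postal contact". The Outcomes section agrees: "after 9 weeks of intervention (T1) at the study center, and after a 3-month follow-up period (T2) by mail services". The Study Design section puts both arms at the study center at baseline. The intervention arm attends its first session there, and for the control arm "The control group (n=100) will meet at baseline at the study center to receive information material". At week 9, "all participants (intervention and control group) will visit the study center after 9 weeks of intervention for a joint conclusion". The center is located in the affiliated social sector institution.

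**Type of outcome.** "The effectiveness of the DHI will be evaluated by self-reported questionnaire assessment in German at baseline (T0") and at the two later times. The instruments are a physical activity questionnaire and a food frequency questionnaire, and both are self-reported throughout.

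**Analysis.** To investigate the impact of the intervention, "differences between the 3 data collection times (T0, T1, and T2) and between the 2 groups (intervention vs control) will be analyzed". Time differences go to repeated-measures ANOVA with Bonferroni post hoc comparisons, or to the Friedman test with Bonferroni correction. The groups are compared at a single time point by a two-tailed t test or a Mann-Whitney U test.

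**Limitations.** The article concedes that "the effectiveness of the intervention is based on questionnaires and, therefore, might be underlying a reporting bias". It does not mention that the setting changes between T1 and T2.

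**The concern.** The setting changes once, and exactly between T1 and T2. Before the change, participants report diet and activity at the institution that recruited them. After it, they report from a mailed form. If reporting differs between these settings, the difference appears as a time effect from T1 to T2, and again from T0 to T2.

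The plan uses differences over the three times as part of its evidence of impact, and the Results section of the article lists individual effects of the intervention period beside the differences between arms. T2 is the only measurement after the intervention ends. A fall from T1 to T2 could be taken as a lost effect and a flat line as a lasting one, when part of either may come from the change of setting. Nothing in the analysis text limits that reading.

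**Working it through.** **1. The plan's own figure.** Inputs from the Statistical Analysis section: d = 0.5, alpha .05 two-sided, power .80, 64 per group. With noncentrality 0.5 × √(64/2) = 2.83 on 126 df, exact power is 0.801; at 63 per group it is 0.795. The stated 64 per group (128 in total) reproduces and is not in dispute. It supplies the n used below.

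**2. Which contrasts cross the change of setting.**

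| Contrast | Settings compared | Confounded with setting? |
|---|---|---|
| T0-T1 over time | center, center | No |
| T1-T2 over time | center, mail | Yes |
| T0-T2 over time | center, mail | Yes |
| Arms at T1 | center, center | No, if any setting effect is equal in both arms |
| Arms at T2 | mail, mail | No, if any setting effect is equal in both arms |
| Arm difference in T0-T2 change | center to mail in both arms | No, if any setting effect is equal in both arms |

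**3. Size for the within-arm T1-T2 test.** The documents give neither a setting effect nor a correlation between times, so both are assumptions shown as ranges: a shift m of 0.1 to 0.3 SD and a correlation r of 0.5 or 0.7. The further assumptions are no true change, 64 completers in the arm, the parametric route, and Bonferroni over three time pairs, .05/3 = .0167.

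- SD of the difference = √(2(1 − r)): 1.000 at r = 0.5 and 0.775 at r = 0.7.
- Noncentrality = m × √64 / SD of the difference; 63 df; two-sided critical value 2.46.

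| Shift m | Noncentrality, r = 0.5 | Significant | Noncentrality, r = 0.7 | Significant |
|---|---|---|---|---|
| 0 | 0 | 1.7% | 0 | 1.7% |
| 0.1 SD | 0.80 | 5.4% | 1.03 | 8.3% |
| 0.2 SD | 1.60 | 20.3% | 2.07 | 35.4% |
| 0.3 SD | 2.40 | 48.1% | 3.10 | 73.7% |

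**4. Effect on the comparison of arms.** With the same 0.3 SD shift in both arms, the two-sided t test at T2 (64 per arm, alpha .05, 20,000 simulated trials) rejects a true null in 5.0% of trials, which is nominal. If the setting effect differs between arms by δ, the noncentrality is δ × √(64/2):

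- δ = 0.1 SD: 0.57, and the test rejects in 8.7% of trials.
- δ = 0.2 SD: 1.13, and the test rejects in 20.2% of trials.

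Nothing in the documents gives δ or shows that it differs from zero.

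**The case against.** **The instruments do not change.** Both are self-reported at all three times, and no part of the article says that staff ask the questions, help with them or read the answers. This stands. What the documents establish is a change of setting and route of return, not a switch from interview to self-completion. It narrows the likely mechanism but does not separate setting from time.

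**The safeguard is already in the plan.** Groups are to be compared at single time points, and a shift common to both arms cancels. This also stands, and it is why the fix is small. But the time tests sit beside the group tests with no order of priority, so the confounded contrasts remain usable as evidence.

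**Within-arm change is weak evidence anyway.** Season, attrition and regression to the mean affect it whatever the setting. That is true, and it supports the same remedy.

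**The size is illustrative.** The shift and correlation are assumed, the expected postal return at T2 is not given, and the Friedman route is not covered. At the low end the error rate is only 5% to 8%.

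**A stronger reading to avoid.** A reader might infer that the comparison of arms is itself biased, because intervention participants were coached at the center and may feel more pressure there to report healthy behavior. The documents do not show this. Participants know their allocation, so such pressure could persist on a mailed form. The Discussion says the target group generally has daily appointments at these institutions, so the place is not peculiar to the coached arm.

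**Conclusion.** The point holds for change over time. T1-T2 and T0-T2 contrasts cannot distinguish a change in behavior from the change of collection setting, and the plan tests both as evidence of impact. Under the stated assumptions, the within-arm T1-T2 test is significant in about 5% to 74% of trials with no true change, against 1.7% nominal. That range is only as good as the assumed shift and correlation; neither its size nor its direction can be taken from the documents.

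T0-T1 change is not affected by this problem. The between-arm comparison at T2 keeps its nominal level unless the setting effect differs by arm, which remains a possibility and not a finding. No stated figure is wrong. This is a moderate weakness in how the follow-up result can be interpreted.

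**What to change.** In the Statistical Analysis section, state that the T2 conclusion rests on the intervention-control difference at T2, or on the arm difference in change from baseline to T2. State that within-arm T1-T2 and T0-T2 changes are reported descriptively and are not evidence of a lasting or lost effect. In the Limitations, add that the collection setting changes between T1 and T2.

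**Cost.** A few sentences and no new data; this can be adopted before analysis even though recruitment has begun. The trial gives up any confirmatory within-arm statement about change after T1.

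**Optional.** Having participants complete the same form at the center unaided and hand it in sealed would reduce any staff influence. It would not remove the change of place. Introduced after recruitment started in March 2022, it could also leave some participants with T0 and T1 collected differently, which would disturb the one time contrast that is now consistent. It is therefore not needed for the main fix.

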#### Statistical Analysis

Sample size calculation was conducted using G*Power (version 3.1.9.7, Heinrich Heine University Duesseldorf). As shown in a meta-analysis by Duan et al [54], the postintervention effect sizes of nutrition- and physical activity–related outcomes in patients with noncommunicable diseases in the intervention and control groups range widely from −1.11 to 6.40 (mean 0.85, SD 1.48) and −0.13 to 4.78 (mean 0.78, SD 1.77), respectively. As we suggested a lower adherence and thus a lower effect size in the targeted group in this study (long-term unemployed), we assumed the effect to be of medium size (Cohen *d*=0.5). With an alpha error of .05 and a power (1-β) of .80, a total sample size of 128 participants (n=64 per group) was calculated. In addition, a previously conducted pretest showed a high dropout of participants of approximately 33% after 9 weeks of treatment, defined as participants who did not reach the “action” phase according to Prochaska et al [33]. Thus, to take further potentially high dropout rates into account, we aim to include a total of 200 participants (n=100 per group) in this study.

To investigate the impacts of the intervention on the self-reported health outcomes assessed by the questionnaire, differences between the 3 data collection times (T0, T1, and T2) and between the 2 groups (intervention vs control) will be analyzed. To test for normal distribution, all data will be subjected to the Kolmogorov-Smirnov test. In case of normal distribution and homoscedasticity of variance (Mauchly’s sphericity test), time-dependent differences will be analyzed by repeated measurement analysis of variance with post hoc comparison by Bonferroni test. In case of nonparametric data, the Friedman test will be used, and the significance level will be corrected using Bonferroni correction. If a normal distribution is given, the differences between the 2 groups at 1 time point will be compared by 2-tailed *t* test. Otherwise, the data will be analyzed by Mann-Whitney *U* test. All differences will be considered statistically significant with *P* values <.05. Statistical analysis will be conducted using SPSS Statistics (version 28, IBM Corporation).

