## Results

The anticipated data will show whether the blended intervention can improve the nutritional or physical activity behavior of long-term unemployed in the rural areas of Germany. Individual effects of the intervention period and differences between the intervention and control groups will be elucidated. Furthermore, data on the use of the mobile app will show the adherence of the target group. In addition, the usability and acceptance of the mobile app will be evaluated.

Study enrollment started in March 2022. Study completion is due at the end of 2022. The first study outcomes are expected to be available in the spring of 2023. The data will be published in international peer-reviewed journals.

The study is part of the project “eHealth solutions to promote dietary and physical activity behaviors among the long-term unemployed in rural areas,” which is funded by the Federal Ministry of Education and Research (BMBF) since 2019 until 2023 (after a COVID-19 pandemic–related extension).

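### The planned between-arm test is valid but ignores the baseline value, and the time tests listed beside it do not test the intervention effect

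*Protocol article*

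**What the plan says.** The Statistical Analysis section says that the effect of the intervention on the questionnaire outcomes will be studied through differences between the three collection times and between the two groups. It then names a test for each.

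- **Time:** "time-dependent differences will be analyzed by repeated measurement analysis of variance with post hoc comparison by Bonferroni test". Non-normal data go to the Friedman test with Bonferroni correction.
- **Group:** if the data are normal, "the differences between the 2 groups at 1 time point will be compared by 2-tailed" t test; otherwise Mann-Whitney U.

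No group-by-time interaction, comparison of change, ANCOVA or other use of T0 in a between-arm test is stated. The Results section keeps the same two parts: "Individual effects of the intervention period and differences between the intervention and control groups will be elucidated".

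The sample size belongs to the group comparison. For the effect, "we assumed the effect to be of medium size" (Cohen d = 0.5). The calculation continues: "With an alpha error of .05 and a power (1-β) of .80", and "a total sample size of 128 participants (n=64 per group) was calculated".

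**The concern.** In a randomised trial the intervention effect is the difference between arms. The plan has one set of tests that compares arms and one that does not, and it presents both as ways of studying that effect without ranking them. Two things follow.

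1. **Precision.** T0 is measured in both arms. A raw comparison at T1 leaves in the error term all the variation that T0 could explain.
2. **Attribution.** A change over time can arise without the app. Both arms receive brochures, recruitment may run from March to the end of 2022 and so spans seasons, and T2 is answered by post whereas T1 is completed at the study centre. A time test that pools the arms tests time. A time test run within each arm invites a comparison of two P values, which is not a test of the difference between arms.

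**Working it through.** **Inputs from the Statistical Analysis section:** d = 0.5, alpha .05, power .80, 64 per group. The group test is two-tailed. **Assumed, because the article does not give it:** a T0-T1 correlation r of 0.3, 0.5 or 0.7.

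**Step 1: reproduce the plan's figure.** Normal approximation: n per group = 2 × (1.960 + 0.842)² / 0.5² = 62.8, so 63. The exact two-sample t calculation gives 63.77, so 64 per group and 128 in total, with power 80.1%. A one-sided test would need about 51 per group, so 64 is a two-sided figure. The stated size is correct for a raw comparison at one time point.

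**Step 2: adjust for T0.** ANCOVA multiplies the residual variance by 1 − r², so the effective standardised difference is 0.5 / √(1 − r²). The table uses the exact two-sample t calculation.

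| r | 1 − r² | Effective d | Power at 64 per group | n per group for 80% |
|---|---|---|---|---|
| T0 not used | 1 | 0.500 | 80% | 64 |
| 0.3 | 0.91 | 0.524 | 84% | 59 |
| 0.5 | 0.75 | 0.577 | 90% | 49 |
| 0.7 | 0.51 | 0.700 | 98% | 34 |

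**Step 3: why ANCOVA and not a change score.** A change-score test multiplies the SD by √(2(1 − r)). By the normal approximation its power at 64 per group is 67% at r = 0.3, 81% at 0.5 and 95% at 0.7. Below r = 0.5 it is worse than ignoring T0.

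**Step 4: time tests read arm by arm.** Suppose that there is no true difference between arms and that both change by the same amount from T0 to T1. Take 64 per arm, a paired t test in each arm, and alpha = .05/3 = .0167 (Bonferroni for three pairs of time points). If p is the power in one arm, the chance that the intervention arm is significant and the control arm is not is p(1 − p).

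| Common change (SD of the change score) | p | p(1 − p) |
|---|---|---|
| 0.10 | 0.054 | 5% |
| 0.20 | 0.203 | 16% |
| 0.25 | 0.330 | 22% |
| 0.30 | 0.481 | 25% |
| 0.40 | 0.768 | 18% |

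The largest value that p(1 − p) can take is 25%, at p = 0.5. The SD of the change score equals the SD of the outcome only when r = 0.5.

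**Choice of n.** Steps 2 to 4 use the stated 64 per group. Taking 33% off 100 would give 67, but the pretest dropout was defined as not reaching the action phase. That is not a missing T1 questionnaire and has no meaning in the control arm.

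**The case against.** The strongest defence is that a proper randomised comparison is already planned. At T1 the t test or Mann-Whitney test holds its type I error. The raw difference in means is unbiased, and in expectation it equals the between-arm difference in change. Chance imbalance at baseline is already covered by the error rate. The trial was sized for this test and the sizing is right. All of this stands. The gain from T0 is efficiency forgone, not a shortfall against the stated 80%, and at r = 0.3 it is only about four points.

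A reader might infer three stronger things that the article does not support.

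- **That effectiveness rests on within-arm tests.** The article does not say that the ANOVA is run per arm. Its opening sentence names both times and groups, so an ANOVA with group as a factor is conceivable. The fair statement is that no such factor is stated and that the Friedman branch cannot have one.
- **That significance in one arm only will be read as an effect.** The article nowhere says so, and the Results section lists group differences in their own right.
- **That season and postal follow-up bias the group test.** They apply to both arms alike and weaken only the time tests.

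Nor can the point be set aside as detail left to an analysis plan. The article names the tests, the rule for switching between them and the significance threshold, and the point concerns those stated choices.

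**Conclusion.** The point holds as a should-fix. The planned T1 comparison is sound, so the trial is not without a legitimate test of its question. As stated, that comparison ignores T0, and power at 64 per group could be 84% to 98% instead of 80% if r lies between 0.3 and 0.7. The size of the gain rests wholly on that assumed correlation, and on d = 0.5 being defined on the raw SD.

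The risk of false attribution comes from the time tests alone, and only if they are read arm by arm. For a common change of 0.1 to 0.3 SD of the change score it runs from 5% to 25%. The upper figure is a mathematical ceiling, not an expected rate. What makes the risk worth closing is that the article does not say which set of tests carries the effectiveness claim.

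**What to change.** Replace the raw group comparison by an ANCOVA of the T1 value, and likewise the T2 value, on arm and T0 value. An equivalent mixed model for both visits, with T0 as covariate and an arm-by-visit term, would also serve. Report the adjusted mean difference with its 95% confidence interval. Use robust or bootstrap intervals where minutes or servings per day are skewed, so that non-normal data no longer lead to a test that cannot adjust for T0. State that the tests over time are descriptive and support no claim of effectiveness.

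The cost is a few sentences in the analysis section. No new data and no larger sample are needed, and SPSS, the software already named, fits these models. The change should be fixed and dated before outcome data are compared by arm.

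### Between-group tests on every outcome at T1 and T2 are each judged at P<.05 with no deciding comparison, although the sample size is for a single .05 test

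*Protocol article*

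**What the plan says.** The Outcomes section describes self-reported measures at baseline (T0), after the 9-week intervention (T1) and after a further 3 months (T2). The activity questionnaire yields minutes per day of sitting, moderate activity and vigorous activity. On diet, "The FFQ consisted of 68 questions regarding the consumption frequency and portion sizes of food items in the past 4 weeks". Intakes are to be "expressed as servings of the consumed food item per day, and a food-based diet quality score will be analyzed". None of these is called primary, and neither T1 nor T2 is given precedence.

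The Statistical Analysis section gives three relevant rules:

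- **Between groups:** if the data are normal, "the differences between the 2 groups at 1 time point will be compared by 2-tailed" t test; otherwise the Mann-Whitney U test is used.
- **Across time:** "time-dependent differences will be analyzed by repeated measurement analysis of variance with post hoc comparison by Bonferroni test"; for nonparametric data the Friedman test is used with a Bonferroni-corrected level.
- **Threshold:** "All differences will be considered statistically significant with" P values under .05.

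The same section bases the sample size on one comparison. On effect size, "we assumed the effect to be of medium size" (d = 0.5). Then: "With an alpha error of .05 and a power (1-β) of .80, a total sample size of 128 participants (n=64 per group) was calculated". Enrolment is set at 100 per group to allow for about 33% dropout.

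**The concern.** A two-arm trial shows effectiveness through its between-group comparison. Here there are several such comparisons, each tested at .05, and nothing says which one decides. The plan does consider multiplicity, but it applies the correction to the contrasts over time and leaves the between-group family uncorrected.

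The Results section asks whether the intervention can improve nutritional or physical activity behaviour. The Conclusions section links a finding of effectiveness to use in community health systems. Under the rule as written, one P<.05 on any outcome at either visit could be reported as effectiveness. The alpha of .05 in the sample size calculation would then not be the error rate of that claim.

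**Working it through.** **1. The plan's own figure.** Inputs from Statistical Analysis: d = 0.5, alpha .05, power .80, two groups of equal size. For a two-sided two-sample t test, the noncentral t calculation gives n = 63.77, so 64 per group and 128 in total, with power 0.801. This reproduces "a total sample size of 128 participants (n=64 per group) was calculated". A one-sided test would need about 51 per group and does not match. The stated size is therefore for one two-sided test at an undivided .05.

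Dropout: 64 / (1 − 0.33) = 95.5, so 96 per group, which the planned 100 covers. If 33% are lost from 100, 67 remain and power is 0.82. The plan defines its 33% by progress in the app, not by missing questionnaires, so 67 analysable participants per group is a working assumption.

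**2. Number of between-group tests.** The outcomes that are certain are sitting, moderate activity, vigorous activity and the diet quality score: 4. Post-baseline visits: T1 and T2. So k = 4 × 2 = 8.

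**3. Chance of at least one P<.05 when nothing differs.**

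Independent tests, either direction: 1 − (1 − 0.05)^k.

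- k = 4 (T1 only): 1 − 0.95^4 = 0.185
- k = 8: 1 − 0.95^8 = 0.337

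Independent tests, results favouring the intervention only: 1 − (1 − 0.025)^k.

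- k = 8: 1 − 0.975^8 = 0.183

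Outcomes in the same people are correlated, and the documents give no correlations. I assumed a range and simulated eight equally correlated normal test statistics, each signed so that positive means benefit:

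| Correlation | Any P<.05 | Favouring the intervention |
|---|---|---|
| 0 | 34% | 18% |
| 0.3 | 30% | 15% |
| 0.5 | 25% | 13% |
| 0.7 | 19% | 10% |

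The nominal rates for a single test are 5% and 2.5%.

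**4. What the Bonferroni correction covers.** Both mentions concern differences between T0, T1 and T2. Neither changes the threshold of a between-group test at T1 or T2, so the table stands.

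**5. Power under the two remedies (d = 0.5, t test).**

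| Per group | One primary at .05 | First Holm step at .025 |
|---|---|---|
| 64 | 80% | 71% |
| 67 | 82% | 73% |
| 100 | 94% | 90% |

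For 80% power at .025, 78 per group are needed; 78 / 0.67 = 116.4, so 117 would be enrolled per group, against the planned 100.

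Adjusting for the baseline value raises the effective effect size to d / √(1 − r²). With r = 0.3 it is 0.5 / √0.91 = 0.524, giving 78% power with 67 per group at .025. With r = 0.5 it is 0.5 / √0.75 = 0.577, giving 86%. Both values of r are assumptions.

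**The case against.** The strongest reply is that this is a condensed article, and that an outcome hierarchy and a multiplicity plan may stand in a full protocol or analysis plan that is not shown. The absence of a named primary outcome would be weak ground on its own. But the article states a significance rule and says where correction applies, and followed as written it leaves the between-group tests uncorrected. That is a rule fixed badly, so the point remains.

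Several stronger readings are tempting, and the documents do not support them:

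- *That every difference is uncorrected.* The comparisons across T0, T1 and T2 are Bonferroni-corrected.
- *That a false claim of effectiveness is likely.* For eight tests the risk is 19% to 34%, or 10% to 18% in the intervention's favour: well above nominal, but below one half.
- *That the error exceeds 50%.* Independent tests reach this at k = 14 (1 − 0.95^14 = 0.512), which would require adding, for example, drinks, fruit and vegetables, and whole grains at both visits. Those are aims within the app; the Outcomes section does not list them as endpoints.
- *That 68 food items are tested.* The 68 questions cover both frequency and portion size, so they are not 68 items. Servings per day may also be only the unit of expression. Item-level testing is possible, but the plan neither states it clearly nor gives a count.
- *That success in either domain is settled as the criterion.* The Results section says nutritional or physical activity behaviour; the Objective and Conclusions join the two with "and". If both domains had to succeed, error would not inflate across domains in this way. Several outcomes within the activity domain, and two visits, would still be open.
- *That the sample size is miscalculated.* It is correct for one comparison.

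**Conclusion.** The point holds in a limited form. Between-group tests on at least four outcomes at two visits are each judged at .05, none is named as deciding, and the stated correction does not reach them. For these eight tests the chance of at least one false positive is about 34% if independent and 19% to 30% at correlations of 0.7 to 0.3. Counting only results that favour the intervention, it is 18%, or 10% to 15%. Testing food items as well would raise these figures by an amount that the documents do not allow one to calculate.

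The figures rest on a count of eight, on equal correlation between the test statistics (an assumption, hence the range), and on a reading in which any one significant outcome could support the claim.

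**What to change.** Before the data are analysed, name T1 as the deciding time point and choose one of the following:

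- **(a) One primary outcome** at two-sided .05. This keeps the stated power (80% with 64, 82% with 67 per group) and needs no more participants.
- **(b) One primary outcome per domain**, from those already collected (for example the diet quality score and an activity-minutes measure), tested by Holm at an overall two-sided .05. Restate power at the .025 step: 71% with 64, 73% with 67, 90% with 100 per group. A baseline-adjusted comparison would give 78% to 86% with 67 per group if the baseline correlation is 0.3 to 0.5. It would have to be written in, since the plan now specifies t or Mann-Whitney tests.

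Replace the blanket P<.05 sentence so that the threshold applies only to the named comparison or comparisons. Make all other outcomes, and all T2 results, secondary: report them as estimates with confidence intervals and without a claim of effectiveness. State also whether success means one domain or both.

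Option (a) costs only wording. Under either option fewer outcomes can support a claim. Under (b), power may fall below 80% after dropout, and recovering it by adjustment depends on a correlation that the documents do not give.
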